#### Other implementation outcomes

2.5.2

To measure other variables in our logic model, the implementer survey will ask about the acceptability, appropriateness, and feasibility of implementing the HSRC initiative (39). We will also assess school characteristics related to the implementation of the HSRC initiative (e.g., school culture, leadership engagement, resources) using an existing measure of the inner setting from the Consolidated Framework for Implementation Research (40). Existing validated measures will also be modified to evaluate implementers’ perceptions of the HSRC initiative (e.g., knowledge, attitudes, and self-efficacy) (41). To determine if HSRC programming had any effect on implementer health behaviors, implementers (e.g., principals, teachers, extension agents, and support staff involved with HSRC’s delivery) will be asked about their physical activity and eating behaviors (42, 43).

#### Primary effectiveness outcomes

2.5.3

Primary effectiveness outcomes include metabolic syndrome, cardiovascular fitness, fruit and vegetable consumption, and body mass index.

##### Metabolic syndrome

2.5.3.1

The International Diabetes Federation defines MetS in children aged 10–16 years old as having a waist circumference above the 90th percentile for a child’s sex and age, and at least two of the four following criteria: triglycerides ≥ 1.7 mmol/L, HDL-C < 1.03 mmol/L, systolic blood pressure ≥130 mmHg or diastolic blood pressure ≥ 90 mmHg, and glucose ≥5.6 mmol/L or known diabetes (3). To assess MetS risk factors, we will measure waist circumference at the midpoint between the floating rib and iliac crest (44). For blood pressure, we will use an automated Omron sphygmomanometer and an appropriately sized cuff to measure blood pressure on children’s upper right arm after they have been seated for 5 min (45). Both waist circumference and blood pressure measurements will be taken up to three times, and the two closest measurements will be averaged. To measure triglycerides, HDL-C, and glucose, we will use a portable CardioChek Plus analyzer to collect a single capillary blood sample following an overnight fast. MetS will be evaluated as binary (i.e., yes or no) and continuous (i.e., number of MetS risk factors) outcomes.

##### Cardiovascular fitness

2.5.3.2

We will determine cardiovascular fitness using the Progressive Aerobic Capacity Endurance Run (46). A research team member will lead the children through the test to provide instructions and pacing, after which, children will complete the test in groups of five or six. Children will run back and forth 20 m, with an initial running speed of 8.5 km/h and a progressive 0.5-km/h increase in running speed every minute thereafter. Number of laps completed will be used in conjunction with age, height, weight, and biological sex to estimate cardiovascular fitness (i.e., VO2 max) using a standardized estimation equation.

##### Fruit and vegetable consumption

2.5.3.3

We will estimate children’s fruit and vegetable intake using a Veggie Meter, a non-invasive portable device that measures skin carotenoid levels (i.e., a biomarker of fruit and vegetable intake) (47). We will collect up to three readings per child and average the two closest measurements.

##### Body mass index (BMI)

2.5.3.4

We will measure BMI by collecting children’s height using a Seca stadiometer and weight using a Tanita body composition analyzer. We will take up to three measurements and average the two closest measurements. We will calculate BMI percentile using the standard formula (kilogram per meter squared) and normative values from the Centers for Disease Control growth charts (48).

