## Introduction

1

In the United States, approximately one in three youth are overweight, and 85% of overweight youth have at least one metabolic syndrome (MetS) risk factor that increases their chance of developing chronic diseases (e.g., cardiovascular disease, diabetes) (1, 2). In 2000, the prevalence of MetS in the United States was about 6.4%; however, the prevalence rate among obese children has been found to be as high as 50% (3). Given that the rate of body mass index (BMI) acceleration doubled during the COVID-19 pandemic, the prevalence of MetS in youth is also likely to increase in the coming years (4).

Established by the U. S. Department of Health and Human Services, The Community Preventive Services Task Force has identified the delivery of school based physical activity and nutrition evidence-based programs (EBPs) as an effective approach for improving obesity, and consequently, MetS and other chronic disease risk factors among youth (5–8). Schools are also a critical setting to improve health behaviors (i.e., physical activity and nutrition), as almost 57 million U. S. children and adolescents attend school, spending an average of 6.5 h there each day (9). Experts recommend that schools help students achieve 30 min of daily physical activity, eat ≥2 vegetables, and a fresh fruit each day, but these goals are rarely met (10, 11). Accordingly, the delivery of more EBPs that promote physical activity and fruit and vegetable consumption are essential for changing youths’ MetS risk.

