#### Statistical and power analysis

2.6.1

This is an optimization study to screen and refine components of a support strategy for the HSRC initiative in preparation for a fully powered randomized controlled trial; thus, this study is not fully powered to examine differences in implementation or effectiveness outcomes (60). To analyze outcomes, we will use univariate and bivariate statistics to determine the distribution of outcome measures and to identify relevant covariates (61). To test between-implementation strategy differences on implementation and effectiveness outcomes, students at schools with and without each implementation strategy (independent variable) will be evaluated using a generalized linear model framework. Baseline scores will be added as a covariate (when applicable), post-intervention score is the outcome, and school is a clustering variable (62). Other covariates (e.g., school size), identified in the preliminary bivariate analyses, will also be included in the model. If missing data occurs, we will mitigate potential biases by analyzing multiple imputed datasets under an intention-to-treat approach (63). Analyses will be compared to per-protocol analyses (64). Interaction effects between strategies are normally small in behavioral trials; however, we will review plots of combinations of strategies to determine if a specific combination of strategies warrants further evaluation. If so, we will add an interaction term to our model. We will calculate standardized effect estimates for each strategy (i.e., Cohen’s *d*), compare effect estimates to make decisions about which components to include in the final support strategy, and report these estimates in our results.

As the goal of this project is to refine and optimize implementation strategies for testing in a future trial, we will conduct an interim analysis following the first cohort of schools using the approach outlined above. This analysis will be repeated following the second cohort of schools. Depending on the results of the interim analysis and potential changes to the strategies that result from the interim analysis, we will conduct a pooled analysis across both cohorts, unless the implementation strategies undergo substantive modifications between cohorts, in which case we will only report the individual results from each cohort.

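### BMI is derived only as a percentile, which compresses change in high-BMI children; a z-score or adjusted raw BMI would be a cheap, modest improvement

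*Protocol article*

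**What the plan says.** BMI is one of four primary effectiveness outcomes (section 2.5.3): "Primary effectiveness outcomes include metabolic syndrome, cardiovascular fitness, fruit and vegetable consumption, and body mass index". Table 3 also marks it as primary. Section 2.5.3.4 describes the height and weight measurements and then gives the only derivation: "We will calculate BMI percentile using the standard formula (kilogram per meter squared) and normative values from the Centers for Disease Control growth charts". The article names no z-score, no percentage of a reference percentile and no analysis of raw BMI.

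Section 2.6.1 sets the model: "Baseline scores will be added as a covariate (when applicable), post-intervention score is the outcome, and school is a clustering variable". The result for each strategy is expressed as Cohen's d, and the investigators will "compare effect estimates to make decisions about which components to include in the final support strategy". That section does not restate the BMI scale, so the percentile is the only scale the article fixes.

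On where the risk lies, the Introduction says that "85% of overweight youth have at least one metabolic syndrome (MetS) risk factor" and that "the prevalence rate among obese children has been found to be as high as 50" per cent, against about 6.4% overall. The definition in section 2.5.3.1 makes "having a waist circumference above the 90th percentile" for sex and age a required criterion.

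**The concern.** A percentile cannot exceed 100, and its slope against the underlying standardised value falls towards zero in the tail. In a linear model of post score on baseline, a given standardised change in a child with obesity therefore counts for much less than the same change in a child of average BMI. The trial's stated interest is in metabolic syndrome, which the article itself ties to overweight, obesity and a large waist. The chosen scale is thus least sensitive where the trial most wants to see change.

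Two things are at stake: some precision in a study of about 320 students that is already declared not fully powered, and the relative size of the effect estimates used to keep or drop strategies.

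**Working it through.** The article gives no power, precision, SD or ICC figure for BMI, so there is no stated figure to reproduce.

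**Step 1: compression (arithmetic only).** With percentile = 100·Φ(z), the slope in z is proportional to φ(z). A fall of 0.2 z moves the percentile by 100·[Φ(z) − Φ(z − 0.2)]:

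| Starting percentile | z | Slope relative to median | Points for a 0.2 z fall |
|---|---|---|---|
| 50th | 0 | 1.00 | 7.9 |
| 85th | 1.036 | 0.58 | 5.2 |
| 95th | 1.645 | 0.26 | 2.4 |
| 99th | 2.326 | 0.07 | 0.7 |

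The same z change is recorded at about one third of its median size at the 95th percentile (2.4/7.9) and about one twelfth at the 99th (0.67/7.93).

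**Step 2: assumed inputs.** From the article: about 20 students per school, and the baseline-adjusted model. Assumed, because the article gives none of them: baseline z with mean 0.5-0.8 and SD 1.1, pre-post correlation 0.90-0.97, strategy effect 0.15 z, and school ICC of 0, or 0.02-0.10 after baseline adjustment. Relative information is the ratio of squared test statistics, percentile against z-score, from large simulated samples.

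**Step 3: every child shifts by 0.15 z.**
- Independent children: relative information is about 0.75-0.83, a loss of about 17-25%.
- School ICC 0.02-0.10: relative information is about 0.81-0.93, a loss of about 7-19%.
- Cohen's d on the total SD: 0.15/1.1 = 0.136 on the z scale, and about 0.131 on the percentile scale.

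A closed form confirms the effect of clustering. If R is the relative information without clustering and ρ the ICC, then with 20 children per school it becomes

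[ρ + (1 − ρ)/20] / [ρ + (1 − ρ)/(20R)].

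- R = 0.75, ρ = 0.02: 0.069/0.0853 = 0.81.
- R = 0.75, ρ = 0.10: 0.145/0.160 = 0.91.
- R = 0.83, ρ = 0.02: 0.069/0.0790 = 0.87.
- R = 0.83, ρ = 0.10: 0.145/0.1542 = 0.94.

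This agrees with the simulated range to within 0.01. The loss shrinks because a school-level shift is compressed in the same way as the strategy effect.

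**Step 4: limiting case, only children at or above the 85th percentile benefit.** Relative information is about 0.2-0.3, and clustering changes this little. Cohen's d falls by roughly half, for example from 0.043 to 0.023 at baseline mean 0.5.

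**Step 5: wider assumptions, no clustering.** With baseline mean 0 to 1.0, SD 1.0 to 1.2, SD of change 0.2 to 0.4 z and effect 0.2 z, relative information is 0.64-0.85 for a uniform shift and 0.18-0.31 in the limiting case. The direction is the same throughout.

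**The case against.** The strongest reply is about size. The trial randomises schools, and once clustering is allowed for, a uniform shift costs only about 7-19% of the information and leaves Cohen's d almost where it was. That stands.

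A reader might go further and infer that a benefit in heavier children would be nearly invisible, or would be read as no effect. The document does not support that. It requires an effect confined to children at or above the 85th percentile, whereas section 3 describes a school-wide walking programme for all students, and the three strategies act on schools and implementers. No section predicts a zero effect in other children. Even in that case d is about halved and does not vanish.

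Other replies carry less weight:
- **Comparability.** Table 1 reports falls in BMI percentile for Walk Across Texas and for Learn Grow Eat and Go. That is a reason to report percentiles descriptively, which the fix keeps.
- **Other outcomes.** Metabolic syndrome, with waist, blood pressure, lipids and glucose, is a separate primary outcome, so high-risk children are not left unmeasured. This limits the consequence but does not make the percentile a good scale.
- **Choice of benchmark.** Measuring loss against the z-score treats an equal z change as an equal change, and z-scores also compress at very extreme BMI. This is fair as a limit on the exact figures; compression at the 95th to 99th percentile remains.
- **Scale left open.** Section 2.6.1 does not name the BMI scale and an analysis plan could choose another. The percentile is nevertheless the only one the article specifies.

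**Conclusion.** The point holds as a minor one. The article fixes the percentile as the only derived BMI variable for a primary outcome, and that scale gives least weight to change in the children in whom the article places metabolic syndrome risk. The compression is arithmetic and needs no assumption about the trial.

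The cost does rest on assumptions about baseline distribution, pre-post correlation and ICC. It is modest for a uniform shift and substantial only if benefit is concentrated in high-BMI children, which is a limiting case and not something the article predicts. It does not follow that a strategy would be misjudged, since several other primary outcomes also inform the choice.

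The attachment of kg/m² to the percentile in section 2.5.3.4 is editorial only; the intended sequence (compute BMI, then reference it to the growth charts) is clear.

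**What to change.** Name the BMI z-score from the same growth charts as the analysed BMI outcome, or raw BMI with baseline BMI, age and sex as covariates. Keep percentiles as description, which preserves comparison with the evidence in Table 1. While editing section 2.5.3.4, let kg/m² define BMI and the growth charts define the age- and sex-standardised value.

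The cost is one derivation. Height and weight (section 2.5.3.4) and age, date of birth and sex (section 2.5.6) are already collected. The downside is small: z-scores also compress at very extreme BMI and are less familiar to school audiences.

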#### Other student outcomes

2.5.4

On the student survey, we will assess several psychosocial constructs (e.g., attitudes, subjective norms, perceived behavioral control) related to physical activity and healthy eating (49–51). Using the Youth Activity Profile, we will also evaluate time spent being active at school, outside of school, and time spent being sedentary outside of school (52). Students will complete a food frequency questionnaire that asks about how frequently they consume 20 different foods and 10 drink categories, which will be used to calculate the SPAN survey’s Healthy Eating Index and its subscales (healthy and unhealthy food index) (53, 54). Finally, we will evaluate students’ engagement in the school and community and several other health-related topics (e.g., sleep) (55, 56).

#### Parent outcomes

2.5.5

To determine if HSRC programming had any effect on parents’ health behaviors, they will complete the 16-item Mediterranean Eating Pattern for Americans screener asking about the frequency at which they eat and drink foods and beverages (57). They will also complete the International Physical Activity Questionnaire to evaluate physical activity in five domains: (1) occupational, (2) transportation, (3) housework, house maintenance, caring for family, (4) recreation, sport, leisure time, and (5) sedentary habits (58). Finally, we will ask several questions to evaluate their engagement in the school and community (59).

#### Sociodemographic measures

2.5.6

Students’ sociodemographic measures will include age, date of birth, biological sex, grade level, race, and ethnicity. Staff’s sociodemographic measures will include their role implementing HSRC, the number of years they have worked at their school, and the number of years they have worked in education. Parents’ sociodemographic measures will include marital status, education, income, and employment.

### Analysis

2.6

#### Statistical and power analysis

2.6.1

This is an optimization study to screen and refine components of a support strategy for the HSRC initiative in preparation for a fully powered randomized controlled trial; thus, this study is not fully powered to examine differences in implementation or effectiveness outcomes (60). To analyze outcomes, we will use univariate and bivariate statistics to determine the distribution of outcome measures and to identify relevant covariates (61). To test between-implementation strategy differences on implementation and effectiveness outcomes, students at schools with and without each implementation strategy (independent variable) will be evaluated using a generalized linear model framework. Baseline scores will be added as a covariate (when applicable), post-intervention score is the outcome, and school is a clustering variable (62). Other covariates (e.g., school size), identified in the preliminary bivariate analyses, will also be included in the model. If missing data occurs, we will mitigate potential biases by analyzing multiple imputed datasets under an intention-to-treat approach (63). Analyses will be compared to per-protocol analyses (64). Interaction effects between strategies are normally small in behavioral trials; however, we will review plots of combinations of strategies to determine if a specific combination of strategies warrants further evaluation. If so, we will add an interaction term to our model. We will calculate standardized effect estimates for each strategy (i.e., Cohen’s *d*), compare effect estimates to make decisions about which components to include in the final support strategy, and report these estimates in our results.

As the goal of this project is to refine and optimize implementation strategies for testing in a future trial, we will conduct an interim analysis following the first cohort of schools using the approach outlined above. This analysis will be repeated following the second cohort of schools. Depending on the results of the interim analysis and potential changes to the strategies that result from the interim analysis, we will conduct a pooled analysis across both cohorts, unless the implementation strategies undergo substantive modifications between cohorts, in which case we will only report the individual results from each cohort.

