### Study setting

2.1

We will recruit two cohorts of eight schools from the North and East regions of Texas to participate in this study. Texas A&M AgriLife Extension defines North and East Texas as a 44-county service area. From west to east, this region includes Cooke, Denton, and Tarrant counties – which includes the Dallas-Fort Worth metroplex – and all other Texas counties east of the Trinity River. From north to south this region includes counties along the Oklahoma border, and extends south to Jasper/Newton counties (a full list of counties can be found at agrilifeextension.tamu.edu/about-2/district-offices-regional-centers/).

Counties in the North and East Texas AgriLife regions have some of the highest rates of cardiovascular disease in the country; and the prevalence of MetS is around 9%. The average rate of cardiovascular disease in these 44 counties is 556.3 deaths per 100,000 people over 18 years of age, which is substantially higher than the average of all Texas counties (442.5 per 100,000 people) and the average of all counties in the United States (432.3 per 100,000 people) (27). The rates in these counties are also higher for deaths from heart disease (430.6 vs. 334.5 in Texas vs. 325.7 in the United States), deaths from stroke (92.14 vs. 80.1 in Texas vs. 75.7 in the United States), and preventable/avoidable deaths from cardiovascular diseases (403.4 vs. 324.6 in Texas vs. 310.3 in the United States) (27). Similarly, these counties also have a higher average prevalence of cardiovascular disease risk factors than the average of other Texas counties, including for high blood pressure (39.1% vs. 37.4% in Texas), high cholesterol (40.0% vs. 39.6% in Texas), diabetes (8.2% vs. 7.9% in Texas), obesity (23.1% vs. 21.4%) leisure time physical inactivity (17.7% vs. 16.1%) and smoking (18.3% vs. 17.0%) (27).

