#### Participant recruitment

2.4.5

We aim to recruit about 20 parents (320 total), 20 students (320 total), and 10 HSRC implementers (160 total) at each school (two cohorts of *n* = 8 schools) enrolled in the study. We will share recruiting materials online (e.g., email) and in-person (e.g., back-to-school events, student drop-off and pickup) to provide details about the study. Parents agreeing to participate will complete the consent form for their child and themselves, a short survey at pre- and post-intervention, and they will be compensated with a $10 gift card at each time point. The research team will meet in-person with children who have received signed parental consent to explain the study and answer any questions. Children will sign an assent form before participating in a survey and biometrics assessment at pre- and post-intervention. They will also receive an item worth $10–$15 (e.g., t-shirt, water bottle, active toy) for each data collection timepoint (pre- and post-intervention). Children who do not agree to participate in the study will still be allowed to participate in HSRC programs. HSRC implementers (e.g., Extension agents, school staff, administrators) will complete a consent form agreeing to participate, a survey pre- and post-intervention, and interviews following the intervention. They will be compensated with a $20 gift card for each survey and $50 for the interview.

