#### Randomization

2.4.6

In each of the two cohorts, schools will be randomized to one of eight experimental conditions and will receive a different combination of implementation strategies (Table 2). In each school year, four schools will receive each implementation strategy, and four schools will not (all schools will receive the website as a constant implementation strategy). Schools and data collectors will be blinded to randomized conditions until a school completes data collection. An interim analysis (following processes outlined below) will be conducted between the two cohorts to determine if implementation strategies should be removed and/or replaced, as well as if any of the current implementation strategies should be modified.

**Table 2 tab2:** Randomized experimental conditions for this study.

Experimental condition	Constant	Factor 1	Factor 2	Factor 3
1	Website/TEKS alignment	None	None	None
2	Website/TEKS alignment	None	None	Enhanced engagement opportunities
3	Website/TEKS alignment	None	School-to-school mentoring	None
4	Website/TEKS alignment	None	School-to-school mentoring	Enhanced engagement opportunities
5	Website/TEKS alignment	Additional resources	None	None
6	Website/TEKS alignment	Additional resources	None	Enhanced engagement opportunities
7	Website/TEKS alignment	Additional resources	School-to-school mentoring	None
8	Website/TEKS alignment	Additional resources	School-to-school mentoring	Enhanced engagement opportunities

Each of the 8 conditions will be randomized one time per cohort.

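### Strategy contrasts rest on 8 or 16 schools: the analysis should fix school-level degrees of freedom, limit screened school covariates at the interim, and weigh Cohen's d with its interval

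*Protocol article*

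**What the plan says.** - **Design.** Study setting (2.1): "We will recruit two cohorts of eight schools from the North and East regions of Texas to participate in this study". Randomization (2.4.6): "In each school year, four schools will receive each implementation strategy, and four schools will not". The note to Table 2: "Each of the 8 conditions will be randomized one time per cohort". So there is one school per factorial cell in each cohort.
- **Sample.** Participant recruitment (2.4.5): "We aim to recruit about 20 parents (320 total), 20 students (320 total), and 10 HSRC implementers (160 total) at each school".
- **Model.** Statistical and power analysis (2.6.1) compares students with and without each strategy in a generalized linear model (the Abstract says general linear model). Baseline is a covariate where applicable, and "post-intervention score is the outcome, and school is a clustering variable". Further covariates, with school size as the example, come from bivariate analyses. An interaction term may be added after plots are reviewed.
- **Decision.** Section 2.6.1 calculates Cohen's d for each strategy, to "compare effect estimates to make decisions about which components to include in the final support strategy". For cohort 1, "we will conduct an interim analysis following the first cohort of schools using the approach outlined above". Section 2.4.6 gives the purpose: "An interim analysis (following processes outlined below) will be conducted between the two cohorts to determine if implementation strategies should be removed and/or replaced".

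The article names no estimator, degrees of freedom or small-sample correction. It does not say how the uncertainty of d enters the interim decision.

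**The concern.** A strategy varies only between schools, so the information about it is counted in schools. With an intercept and three main effects, 8 schools leave 4 error degrees of freedom. Sixteen leave 12, or 11 with a cohort term. Methods for clustered data that rely on many clusters (robust or GEE standard errors, or a random-effect standard error read against a normal reference) can give intervals that are too short at these sizes.

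Two features of the plan add to this. Each screened school-level covariate, and any interaction term added after looking at plots, takes one of the 4 interim degrees of freedom. And the removal or replacement decision is described only as a comparison of estimates that are very imprecise with 4 schools a side.

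The stake is that a useful strategy is dropped, or a null one kept, by chance. If the change is substantive, section 2.6.1 gives up pooling, and the reported results then also rest on 8 schools per cohort.

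**Working it through.** **Inputs from the article.** 8 schools per cohort, 2 cohorts, 4 v 4 schools per strategy per cohort, and 20 students per school. The student total reproduces: 2 × 8 × 20 = 320.

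**Assumptions (not in the article).** Total SD = 1, no attrition, two-sided 95% limits. The ICC is taken as 0.01 to 0.20 for student health outcomes and up to 0.8 for dose.

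**1. Type I error at a nominal 5%.** Null trials of the 2×2×2 design were simulated with 4 school-level parameters and 20 students per school. For the four methods below, results hardly changed across ICCs from 0.02 to 0.8.

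| Method | 8 schools | 16 schools |
|---|---|---|
| Robust SE, normal reference | 22–24% | 11–12% |
| Robust SE with the usual finite-sample factor, t on schools − 1 | 14–15% | 8% |
| School-level SE, normal reference | 11–13% | 7–8% |
| School-level SE, t on schools − 4 | about 5% | about 5% |

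The third row can be checked exactly: P(|t| > 1.96) is 12.2% on 4 df and 7.4% on 12 df.

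**2. Precision of d.** SE(d) = √[(4/K)(ICC + (1 − ICC)/20)] for K schools, and the half-width is SE × t(0.975, K − 4). The multiplier is 2.78 for K = 8 and 2.18 for K = 16. Example with K = 8 and ICC 0.05: √[0.5 × (0.05 + 0.0475)] = 0.221, and 0.221 × 2.776 = 0.61.

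| Assumed ICC | 8 schools (4 df) | 16 schools (12 df) |
|---|---|---|
| 0.01 | ±0.48 | ±0.27 |
| 0.05 | ±0.61 | ±0.34 |
| 0.10 | ±0.75 | ±0.42 |
| 0.20 | ±0.96 | ±0.53 |
| 0.80 | ±1.77 | ±0.98 |

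These figures are before baseline adjustment. If baseline explained half the variance at both levels (an assumption), multiply by √0.5 = 0.71. With 8 schools, ICC 0.05 then gives ±0.43 and ICC 0.20 gives ±0.68.

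**3. Cost of school-level terms at the interim.** As error df fall from 4 to 3, 2 and 1, the critical t goes from 2.78 to 3.18, 4.30 and 12.7. At ICC 0.05, if the added terms explain nothing, the half-width goes from 0.61 to 0.70, 0.95 and 2.81.

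**4. Noise in the comparison of estimates (8 schools).**
- True d = 0.2: the estimate falls at or below zero with probability Φ(−0.2/SE). This is 18% at ICC 0.05 (SE 0.221) and 28% at ICC 0.20 (SE 0.346). With half the variance explained by baseline, 18% becomes 10%.
- Three null strategies: the largest estimate exceeds 0.2 with probability 45% (ICC 0.05) to 63% (ICC 0.20).
- Dose, true d = 0.5, ICC 0.8 (SE 0.636): the estimate is at or below zero in 22% of interims. It fails to rank first against two null strategies in 43%.

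**The case against.** The strongest reply is that the article names no robust error, GEE or normal reference, so the inflated error rates belong to methods it never states. A mixed model with small-sample degrees of freedom is consistent with the text and holds about 5%, and an article may leave that detail to the full protocol or analysis plan. This stands. A reader might infer that the model as written understates error. The text supports only that it can.

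Second, section 2.6.1 says the study is not fully powered and serves to screen and refine strategies before a larger trial. Selecting on estimates is a deliberate feature of an optimization study. This also stands: wide intervals alone are disclosed and are not the fault. The disclosure does not, however, say how the intervals are to be used when a strategy may be dropped.

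Third, a change of reference distribution leaves the point estimates, and hence their ranking, unchanged. That is correct. School-level degrees of freedom alone would not prevent a chance removal, which is why the interval has to be reported and considered in the decision.

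Fourth, removal might seem to break the design of all eight conditions in each cohort. It does not: section 2.4.6 provides for removal and replacement, and section 2.6.1 provides for reporting the cohorts separately.

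Fifth, a rule that a strategy may be removed only if its upper limit lies below some threshold would largely abolish the interim at these interval widths. That would be a debatable redesign of the screening step, and it is not proposed here.

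**Conclusion.** The point holds in limited form and should be fixed. The plan leaves the few-cluster method open where the choice matters. Common large-sample choices give about 12 to 24% type I error with 8 schools and 7 to 12% with 16, while school-level t gives about 5%. The plan also lets bivariate screening add school-level covariates to an analysis with 4 error degrees of freedom. It describes an interim removal or replacement decision as a comparison of d values whose 95% limits are about ±0.5 to ±1.0 SD for health outcomes, and up to about ±1.8 SD for dose.

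The limits rest on assumed ICCs and ignore baseline adjustment, which would narrow them for health outcomes. They apply to 8 schools. With 16 schools the range is about ±0.27 to ±0.53 for health outcomes and ±0.98 for dose at ICC 0.8.

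A reader might take the dose ICC to be near 1 because section 2.5.1 builds dose from what the student's teachers received. That is not established: the Discussion says smaller groups within a school get additional programs, so dose can differ between classes in one school. The ±1.8 figure is conditional on an ICC near 0.8.

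**What to change.** 1. State that every strategy contrast uses school-level degrees of freedom. Any of these would do: a mixed model with Kenward-Roger degrees of freedom; baseline-adjusted school means with t on schools minus school-level parameters; or a permutation test over the allocation. Report each Cohen's d with the matching interval.
2. At the interim, replace the screened school-level covariates with at most one named in advance.
3. State that the interim decision considers these intervals alongside feasibility and acceptability. No fixed upper-limit rule for removal is needed.

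This changes analysis wording only and needs no further schools or data. The cost is wider intervals, which are the correct ones for this number of schools.
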